#### Effects of PA treatment on neuropsychological changes and other secondary outcomes (RQ2) and time course of any improvements (RQ3)

To analyze between-group (PA treatment vs. sham treatment) differences on the secondary outcome measures (see Table 3) across four (RS1-RS4) or six (RS1-LTFU2) time points, we will conduct 2 × 4 or 2 × 6 ANOVAs as described for the analyses of the primary outcomes. Specifically, a 2 × 4 ANOVA will be run on each clinical assessment outcome (limb temperature asymmetry, hands size difference, grip strength and ΔFTP ratios, MDT, MPT, two-point discrimination threshold ratios, and allodynia) and mean group scores in the following computer-based measures: PSSs in the TOJ task, PSEs in the Landmark task, attention bias scores in the Greyscales task, and bias scores in the MNLB task. We will also use 2 × 4 ANOVAS to analyse between-group differences on indices A and B for the affected and unaffected hand performance in the Directional Hypokinesia task, as well as on hand laterality recognition accuracy and RTs indices in the Hand Laterality Recognition task across RS1-RS4. Separate 2 × 6 ANOVAs will be run on mean group scores on each of the self-reported questionnaire measures: pain intensity and interference components of the BPI, the Pain Detect Questionnaire, The BPDS, the Tampa Scale for Kinesiophobia, and the Profile of Mood States.

We will plot group means of daily ratings of average pain, range of movement, and interference over time and use contrasts to identify the time points of significant group differences. We will also identify for both groups and for each measure the average number of days to reach peak improvement from the start of treatment, and the average number of days from the peak improvement to return to baseline.

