The Revised Life Orientation Test [48] assesses levels of optimism and pessimism. Participants rate to what extent they agree with 10 statements on a scale from 0 – “strongly disagree” to 4 – “strongly agree”. The Patient Centred Outcomes Questionnaire [49] is also administered to measure patient-centred expectations and criteria for success in chronic pain treatment. Rating scales from 0 to 10 are used to indicate the usual, desired, expected and considered successful levels of pain, fatigue, emotional distress, and interference with daily activities (0 – “none”, 10 – “worst imaginable”), and the importance of improvement in each of these areas (0 – “not at all important”, 10 – “most important”). The decision to include the Revised Life Orientation Test and the Patient Centred Outcomes Questionnaire in the current trial was driven by the fact that optimism and expectations of outcome have been known to influence the success of novel treatments [70–72]. Thus, it is important to confirm that the two treatment groups are matched on these extraneous factors, or to include these variables as covariates in the analysis of outcome measures if they are not.

The participants keep daily logbooks for weeks 1–11 in which they use 0–10 NRSs to record their average level (over the preceding 24 h) of pain (0 – “no pain at all”, 10 – “pain as bad as it could be”), the range of movement in the affected arm (0 – “no movement at all”, 10 – “normal movement”), and the degree to which their symptoms have interfered with their daily life (0 – “no interference at all”, 10 – “complete interference”). These measures are designed to track the time-course of any change in pain, movement, and interference during the first 10 weeks of the study (i.e. four-week baseline period, two-week treatment period, and four-week immediate post-treatment period).

Finally, the Patient Global Impression of Change questionnaire [50] is administered to measure participants’ impression of how much their symptoms have changed due to treatment. It produces a single rating on a scale from 1 – “no change” to 7 – “a great deal better”. The Patient Global Impression of Change is a widely recommended measure of perceived global improvement and satisfaction with treatment [60, 62].

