### Statistical analyses

To process and analyse the data we will use IBM SPSS Statistics [106], R [107], and MATLAB [108] software. Hypotheses will be tested using a significance level of *α* = .05. We will control type I errors in the primary analyses using Holm-Bonferroni corrections for multiple comparisons within each outcome analysis. No correction for multiple testing will be made in the exploratory analyses. We will report 95% bias-corrected and accelerated (BCa) bootstrap confidence intervals around all mean values.

Outliers are defined as scores outside ±3 SDs from the participant’s mean score for a task condition (participant-level data) or from the group mean (group-level data) for a particular test or task condition. We will examine participant-level and group-level RT data in the Hand Laterality Recognition and Directional Hypokinesia tasks for the presence of outliers and use nearest neighbour replacement if any are identified. We will use the same method of nearest neighbour replacement for the group-level outliers identified on the remaining outcome measures.

T-tests and ANOVAs will be conducted to compare mean values between groups and between data collection time points. Statistically significant interactions will be interrogated through follow-up contrasts. Wilcoxon signed-rank tests and Mann-Whitney U tests will be used if assumptions of t-tests are violated; however, ANOVAs are robust to moderate violations of normality and homogeneity of variance. Therefore, we will use ANOVAs unless severe violations of normality, homogeneity of variance, and sphericity assumptions are present, in which case we will use linear mixed models analyses with bootstrapping procedures.

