#### Sample size and power calculation

The required sample size was calculated based on the primary outcome measure of self-reported pain [109]. A meta-analysis defined a clinically significant reduction in pain as a change of Δ = − 2 (on a scale of 0–10) [110]. The sample size required to detect a pain reduction of this magnitude between RS2 and RS3 was estimated. The risk of type I error was set at 5% and the risk of type II error was set at 10%, giving 90% power to detect a significant change in the pain. The standard deviation expected in the current study was estimated as 1.98 based on pain intensity ratings obtained by our group in recent research [8]. Given these parameters, a minimum of 42 participants with CRPS (21 per group) is required to evaluate the effects of the PA treatment on the primary outcome measure of pain. Taking into account an anticipated drop-out rate of 20%, up to 52 participants with CRPS will be enrolled in order to obtain a total of at least 21 complete datasets for RS1-RS4 per treatment group. To provide normative data, 21 healthy (pain-free) control participants will be recruited.

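### The search of the daily logbook for significant time points falls under no stated multiplicity rule, and the average time to return to baseline is distorted because the logbook ends four weeks after treatment

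*Protocol article*

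**What the plan says.** The logbook plan is in the protocol article's section on RQ2 and RQ3. Group means of three daily 0-10 ratings are plotted, and the investigators will "use contrasts to identify the time points of significant group differences". For each group and measure they will also report the average number of days from treatment start to peak improvement, and "the average number of days from the peak improvement to return to baseline".

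The section Self-report questionnaires sets the span of the logbook: "four-week baseline period, two-week treatment period, and four-week immediate post-treatment period". That is about 70 days, of which 42 follow the start of treatment and 28 follow its end.

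Statistical analyses sets the test level: "Hypotheses will be tested using a significance level of" .05. It applies Holm-Bonferroni to the primary analyses, within each outcome, and no correction to exploratory analyses. The logbook ratings are secondary outcomes and carry neither label. Treatment outcome analyses fills missing logbook days by linear regression. It does not say how a participant who has not returned to baseline when the logbook ends, or who never improved, enters the averages.

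**The concern.** There are two separate problems.

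First, looking along a series of daily ratings for the points where the arms differ significantly is a multiple search. With no error rule attached, some days will cross .05 by chance, and they may be read as the onset or offset of an effect.

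Second, a plain average of days to return to baseline needs a return day for everyone, and observation stops 28 days after treatment. Participants whose benefit outlasts the logbook have no return day. They must either be left out, so that the average rests on early relapsers, or be given the last day as if they had relapsed then. Both choices pull the average down, and more so the longer the benefit lasts. A participant who never improves still has a best day, so noise supplies a peak and a return.

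The stake is the fine-grained account of when benefit appears and how long it lasts.

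**Working it through.** **Inputs from the protocol.** Three measures; 70 logbook days, 42 from treatment start and 28 after treatment; .05 per test; 21 participants per arm.

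**The plan's own figure.** The article gives no figure for the logbook analysis. The sample size, which supplies the 21 per arm, reproduces. With a 2-point difference, SD 1.98, two-sided .05 and 90% power, n = 2 × (1.96 + 1.2816)² × 1.98² / 2² = 20.6, so 21 per arm. Sidedness is not stated; one-sided would give 17.

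**Chance findings if contrasts are made by day.** The expected number of false days does not depend on correlation:
- per measure: 42 × .05 = 2.1, or 70 × .05 = 3.5;
- over three measures: 126 × .05 = 6.3, or 210 × .05 = 10.5.

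The chance of at least one false day does depend on correlation. If days were independent it would be 1 − .95^42 = 88% and 1 − .95^70 = 97% per measure, but ratings by the same person are not independent. Null trials were therefore simulated (1,500 per setting, 21 per arm, daily t-tests). Assumed, not in the protocol: between-person share of variance .5 to .85, day-to-day autocorrelation 0 to .6, and correlation between measures .5.

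| | 42 days | 70 days |
|---|---|---|
| At least one false day, one measure | 21-60% | 25-71% |
| At least one false day, any of three measures | 46-90% | 53-96% |

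The 42-day column is the fairer one, since the four baseline weeks cannot show a treatment effect. Bonferroni or Holm across days lowers the chance to about 1-4%.

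**Duration without daily noise.** Assume exponential return times after the end of treatment with mean μ, observed for 28 days.
- Share returning: 1 − e^(−28/μ).
- Average if non-returners are left out: μ − 28e^(−28/μ) / (1 − e^(−28/μ)).
- Average if non-returners are set to the logbook end: μ(1 − e^(−28/μ)).
- Median: μ ln 2, estimable only if below 28.

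| True mean (days) | Returned by day 28 | Non-returners left out | Set to logbook end | Kaplan-Meier median |
|---|---|---|---|---|
| 14 | 86% | 9.6 | 12.1 | 9.7 |
| 28 | 63% | 11.7 | 17.7 | 19.4 |
| 56 | 39% | 12.8 | 22.0 | not reached |
| 84 | 28% | 13.2 | 23.8 | not reached |

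Worked line for μ = 56: e^(−0.5) = .6065; 56 − 28 × .6065 / .3935 = 12.8; 56 × .3935 = 22.0.

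Tripling the true mean from 28 to 84 days moves the first average by 1.5 days and the second by 6.1.

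**Duration with daily noise, counted from the peak as the protocol does.** Peak is the best of the 42 days from treatment start; return is the first later day at or beyond the baseline mean. Assumed: a 2-point benefit that builds up over treatment and then fades, daily noise SD 1.0 or 1.4, and autocorrelation 0 or .5 (20,000 participants per setting). For true means of 14 to 84 days, both averages fall to about 5-12 days, because a single bad day ends the spell. With no benefit at all, the same rule gives a mean peak at about day 21.5 and about 2-3.5 days from peak to return.

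**The case against.** The strongest reply is that the logbook is a supplement. RQ3 is answered first by all outcomes immediately and 4 weeks after treatment, and by self-reported outcomes at 3 and 6 months. Current pain has planned contrasts of RS2 with RS4, LTFU1 and LTFU2, and the questionnaires have six-time-point ANOVAs. This stands. A reader might infer that the trial cannot tell a long benefit from a short one; the protocol does not support that, because those comparisons do not use the logbook averages.

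A reader might also infer that the plan prescribes 210 uncorrected daily tests. It does not say so. It names neither the unit nor the number of contrasts, and it exempts only exploratory analyses from correction. Since Treatment outcome analyses calls intention to treat the primary analysis, the Holm rule could even be read as wider than the two primary outcomes. Days are the natural reading of time points in daily ratings, but the figures above are conditional on it.

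On duration, the article does not say that non-returners are dropped, and the days could be read from the group curves. The closed-form figures also start at the end of treatment, whereas the protocol counts from the peak. These points limit the exact figures but not the direction: both ways of handling non-returners compress the average, and the noisy calculation that starts at the peak compresses it further. A group curve that has not returned by the last day leaves the same gap.

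Finally, contrast units and the handling of non-returners may be left to an analysis plan that is not shown. That covers missing detail. It does not cover the choice, made in the article itself, of a significance search over daily ratings and a plain average of a time that the logbook can cut off.

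**Conclusion.** The concern holds in limited form. If the contrasts are by day, no stated rule clearly controls them, and the chance of at least one false day is about 21-60% per measure over 42 days, or 25-71% over 70. This rests on the assumed correlations. Higher figures, such as the 88-97% for independent days, require ratings by the same person to be unrelated and should not be quoted as the expected size.

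The average time to return to baseline is a poor measure of duration, but it would be wrong to call it biased low in general. It is biased low when a real benefit exists: 11.7-13.2 or 17.7-23.8 days for true means of 28-84 days, under assumed exponential return times. With no benefit it is biased upward, at about 2-3.5 days. The two errors together narrow the apparent difference between PA and sham.

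The primary RS2-RS3 analysis, the sample size and the RS4 and long-term follow-up comparisons are not affected. The change is worth making because it is cheap and the present statistics would mislead.

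**What to change.** Analyse each logbook measure with one mixed model, Group by Period (or by week, on weekly means), adjusted for the baseline weeks. Report the between-arm difference per period with a confidence interval. Keep the daily plot as description. If day-level claims are wanted, apply Holm across the days and say so.

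Replace the average of days to return with a Kaplan-Meier estimate of time to return to baseline, censored at the participant's last logbook day. Define the time origin, improvement and return in advance, with return defined so that one noisy day does not count. Where fewer than half have returned, report the median as not reached. Label this estimate descriptive: restricting it to participants who improved conditions on a response after randomisation, so the arms are no longer compared as randomised.

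Cost: a change of analysis wording and slightly more programming, with no change to data collection. Unless Holm across days is used, statements that a particular day is significant are given up.

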#### Predictors of the response to PA treatment and/or CRPS progression over time (RQ4)

We will conduct exploratory analyses of the potential factors that can predict response to treatment for the PA group. First, we will calculate reduction scores as a change in current pain scores and CRPS severity scores from the immediate pre-treatment to immediate post-treatment sessions (RS3 – RS2). Second, we will conduct two separate linear mixed models regressions on pain reduction scores and CRPS severity reduction scores including the pertinent explanatory factors such as demographic characteristics; current pain intensity; CRPS severity score; and scores on the self-report questionnaires, clinical assessments, and computer-based tests. In the first instance, we will consider those outcomes that differed the most from the healthy control participants in RS1 (see statistical analyses for RQ5 in the next section).

The same factors will be considered potential explanatory variables in linear mixed models regressions on current pain scores and CRPS severity scores across four research sessions (RS1-RS4). These exploratory analyses will be conducted for data from all the participants with CRPS to examine possible predictors of CRPS progression over time (including but not limited to treatment group).

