While clearly defining our primary outcome measures, the trial includes a wide range of secondary outcome measures to assess the impact of treatment on pain and other clinical CRPS symptoms, as well as neuropsychological and emotional functioning, and symptoms’ interference with daily life. These measures will allow us to explore relationships between self-reported, clinical, and neuropsychological manifestations of CRPS from baseline data, independent of the primary research aim of testing the efficacy of PA.

Despite their informative value, large number of secondary outcomes might reduce the quality of data. To mitigate the potential impact of long duration and burden of research sessions, we composed a battery of assessments that would take no longer than 4 h to complete, including breaks between assessments. We also provide the participants with overnight accommodation near the research centre in cases when long travels are required, to minimise their fatigue during research sessions. In light of how little is known about cognitive changes in CRPS and effects of PA on these changes, broad battery of neuropsychological tests seems appropriate.

Furthermore, this research may identify potential individual differences accounting for the course of CRPS and response to treatment. The findings could provide an indication of how to identify the patients who are most likely to benefit from PA based on their cognitive and physical symptoms. This would inform subsequent research and therapies.

If PA brings benefits beyond that of the sham treatment on the primary outcome measures of the ongoing trial, this treatment should be developed as a recommended method to reduce pain and other CRPS symptoms. The study is likely to expand on our limited understanding of this debilitating condition and its neuropsychological components.

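### RQ4 looks for predictors of response to PA in the PA arm alone, so it cannot tell who benefits from PA from who would have changed anyway

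*Protocol article*

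**What the plan says.** The protocol article, under the heading for RQ4 (predictors of response and of progression), describes two sets of models.

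- **Response.** "We will conduct exploratory analyses of the potential factors that can predict response to treatment for the PA group". The outcome is the RS3 minus RS2 difference, one value per participant for current pain and one for the CRPS severity score. The plan continues: "we will conduct two separate linear mixed models regressions on pain reduction scores and CRPS severity reduction scores including the pertinent explanatory factors". The candidate factors are "demographic characteristics; current pain intensity; CRPS severity score; and scores on the self-report questionnaires, clinical assessments, and computer-based tests". They thus include the two variables from which the change scores are formed. The section does not say whether factor values come from RS1 or RS2. It says that measures which differ most from the healthy controls at RS1 will be considered first.
- **Progression.** The same factors enter models of the RS1–RS4 scores. "These exploratory analyses will be conducted for data from all the participants with CRPS to examine possible predictors of CRPS progression over time", with treatment group as one candidate among others ("including but not limited to treatment group"). No product of a factor with group is named.

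The Discussion says, in conditional terms, that the findings could point to "how to identify the patients who are most likely to benefit from PA based on their cognitive and physical symptoms". Both sets of models are declared exploratory, and the Statistical analyses section states that exploratory analyses are not corrected for multiplicity.

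**The concern.** RQ4 asks what predicts response to PA. Change within the PA arm is a sum of parts: any effect of PA, the natural course of CRPS, the effect of repeatedly moving the affected limb, and regression to the mean. A factor may be associated with any of these. Only the contrast with sham shows whether it is associated with the first.

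The protocol makes this argument itself. The primary research question gives the sham arm the task of separating PA from the added movement. The Background criticises earlier PA studies for having no sham condition. The Design section takes two baselines because symptoms are expected to fluctuate. The response analysis sets the sham arm aside and is not said to use the two baselines.

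At stake is the reading of a secondary, exploratory result. An association seen only in the PA arm could be carried into later work as a marker of who benefits, although it would have appeared just as strongly under sham.

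**Working it through.** **Sample size.** The plan's figure reproduces: n per group = 2 × (1.960 + 1.282)² × 1.98² / 2² = 20.6, rounded up to 21. The PA-only regression therefore has about 21 participants. At n = 21 a correlation is significant at two-sided 5% when |r| exceeds 2.093 / √(19 + 2.093²) = 0.433.

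**Assumptions.** The document gives no correlation between sessions and none between any factor and change. Both are assumed below and shown as ranges. Every PA participant is given the same effect of −2 points, so no factor truly modifies the effect of PA. A constant effect moves only the intercept.

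**1. RS2 level as predictor of its own change.** Let RS2 and RS3 have equal variance σ² and correlation ρ.

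- Cov(RS2, RS3 − RS2) = −(1 − ρ)σ²
- Slope = −(1 − ρ)
- Var(RS3 − RS2) = 2(1 − ρ)σ²
- Correlation = −√((1 − ρ)/2)

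| Assumed ρ | Slope | Correlation with change | Simulated share significant, n = 21 |
|---|---|---|---|
| 0.5 | −0.50 | −0.50 | 67% |
| 0.6 | −0.40 | −0.45 | 55% |
| 0.7 | −0.30 | −0.39 | 42% |
| 0.8 | −0.20 | −0.32 | 29% |
| 0.9 | −0.10 | −0.22 | 16% |

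The nominal rate is 5%. Applying the entry rule of pain ≥2 at RS1 and RS2 changes little (65% at ρ = 0.5, 17% at ρ = 0.9). The shares do not depend on the SD, so the same table holds for the severity score under the same assumptions.

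**2. RS1 level as predictor.** With independent errors at each visit, Cov(RS1, RS3 − RS2) = ρσ² − ρσ² = 0. In simulation the factor is then significant in 4% to 6% of trials. The coupling depends on a choice that the text leaves open.

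**3. A factor that predicts change equally in both arms.** This applies to any candidate, from whichever session.

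| Assumed correlation of factor with change, both arms | PA-only regression significant | Group × factor interaction significant |
|---|---|---|
| 0.3 | 27% | 5% |
| 0.5 | 67% | 5% |
| 0.6 | 86% | 5% |

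**4. The interaction as remedy.** In the setting of step 1, a baseline-by-group interaction using both arms (42 participants) has mean slope about 0 and is significant in about 4% to 6% of trials at every ρ tried. These runs used change as the outcome. With RS2 as the factor, putting RS3 on the left and RS2 on the right gives the same interaction coefficient.

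**5. What the interaction can detect.** Take a factor correlated 0.5 with change under PA and 0 under sham. By Fisher's z, atanh(0.5) = 0.549 and SE = √(1/18 + 1/18) = 0.333, so the ratio is 1.648. Power = P(Z > 1.960 − 1.648) = about 38%.

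**The case against.** The strongest reply is that the work is declared exploratory, with limited evidence and a small sample given as reasons, and that no decision in the trial depends on it. That stands as to weight. It does not answer the point: the label excuses imprecision and uncorrected testing, not an analysis that estimates a different quantity from the one the question names.

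A second reply is that the all-participant models do use the sham data and include treatment group, and that a condensed article need not list every model term. Interactions are indeed neither listed nor ruled out there, and their absence alone would be no finding. But those models are aimed at progression, and the response analysis is explicitly confined to the PA arm.

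A third reply is that the remedy has little power. That is true, and step 5 shows it. A wide interval around the right quantity is still a more honest answer than a significant result for the wrong one.

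Some stronger readings are tempting but unsupported:

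- **That baseline pain will be named as a marker.** This holds only if RS2 values are the predictors, and the size depends on an assumed correlation.
- **That many factors tested singly make a false hit likely.** The article fixes no number of factors and does not say that they are tested one at a time. It plans two regressions, with candidates narrowed first by the comparison with healthy controls.
- **That the mixed model is unusable.** With one change score per participant, a participant random effect cannot be separated from the residual. The fixed effects remain estimable, so the model reduces to ordinary regression. This is mostly a matter of naming.
- **That the trial will select patients on the result.** The Discussion is hedged and speaks of informing later research and therapies.

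**Conclusion.** The point holds in limited form. The response analysis for RQ4, as fixed in the article, identifies predictors of change during PA, not predictors of response to PA.

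For factors that predict change equally in both arms, the false-attribution rate at n = 21 is about 27% to 86% for assumed correlations of 0.3 to 0.6. For the outcome's own RS2 level it is about 67% down to 16% for assumed RS2–RS3 correlations of 0.5 to 0.9, and about nominal if RS1 values with independent visit errors are used. All these figures assume normally distributed scores, equal variances and no true effect modification.

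The defect is confined to a secondary, exploratory question. The RQ1 efficacy analysis is not touched. It is worth correcting because the data for a valid analysis are already being collected.

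**What to change.** - For the response part of RQ4, fit in both arms an ordinary linear model of the RS3 score on the RS2 score, Group, the factor and Group × factor, separately for pain and for CRPS severity. Where the factor is the RS2 score itself, the model is RS3 on RS2, Group and Group × RS2.
- Name a short list of factors before change scores are examined by arm. It may still draw on the RS1 comparison with healthy controls. State whether each factor is taken from RS1 or RS2.
- Report each interaction with its confidence interval, labelled exploratory.
- Limit any statement in the Discussion or results paper about who benefits from PA to these interactions. Present PA-only associations as descriptive predictors of change during PA.
- Replace the term linear mixed model for the single change scores.

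The cost is a few sentences and a few extra model runs, with no new data. The drawback is imprecision: with about 21 per arm, even the marked difference in step 5 would be detected in only about 38% of trials, and the report should say so.
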